### Secondary analyses

Self-report questionnaires and observer ratings will be analyzed by mixed models with repeated measurements. With two co-primary outcomes, we will conduct the tests at a 0.025 level of significance (two-tailed) to adjust for the multiple comparison issue. Further analyses will include cross-sectional analyses to compare therapists; subgroup analyses of subjects’ and therapists’ conditions; and costs of the SP treatment.

Descriptive statistics showing the measurements over time will be presented whenever appropriate. Serious adverse events and cases of drop-outs will be analyzed descriptively.

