**Methods/design:**

Patients are assigned to treatment according to their preference or randomized (if they have no clear preference). Up to 80 sessions of psychodynamic or psychoanalytically oriented treatments (PAT) or up to 60 sessions of CBT are offered during the first year in the study. After the first year, PAT can be continued according to the ‘naturalistic’ usual method of treating such patients within the system of German health care (normally from 240 up to 300 sessions over two to three years). CBT therapists may extend their treatment up to 80 sessions, but focus mainly maintenance and relapse prevention. We plan to recruit a total of 240 patients (60 per arm). A total of 11 assessments are conducted throughout treatment and up to three years after initiation of treatment. The primary outcome measures are the Quick Inventory of Depressive Symptoms (QIDS, independent clinician rating) and the Beck Depression Inventory (BDI) after the first year.

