### Design

The trial will include about 360 chronically depressed outpatients. About 180 patients will have a clear preference foreither PAT or CBT. After baseline assessment (t0) they will be assigned to a study therapist offering the preferred intervention. About 180 patients will come without preference and accept to be randomized to either PAT or CBT. Randomization will take place after baseline assessment (t0). Figure1 summarizes the 2 (preference) by 2 (psychotherapies) by 4 (time) factorial design.

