### Outcome

The primary outcome measures are the Quick Inventory of Depressive Symptoms (QIDS [26]) (independent clinician rating) and the Beck Depression Inventory (BDI-2) one year after initiation of treatment (t4). Treatment response is defined as a decline of at least 50% from t0 (baseline, pre-treatment) to t4 (12 months after intake. Remission is defined by a QIDS-score below 6. A relapse is defined when the criteria of a major depressive disorder (MDD) are fulfilled, for example, a QIDS-score above 9 is documented or hospitalization or outpatient treatment are needed.

Secondary outcome measures include the Beck Depression Inventory (BDI 2 [27]), the QIDS-self-rating, the Symptom-Checklist (SCL-90R [28]), the Depressive Experience Questionnaire (DEQ [29]) and the Dysfunctional Attitude Scale (DAS [30]). Furthermore, we assess social functioning (SOFAS [31]), the Helping Alliance Questionnaire (HAQ [32], and recurrence of depressive episodes assessed by the longitudinal follow-up evaluation interview (LIFE [33]).

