### Sample size calculation

Sample size calculation was based on meta-analyses with similar interventions in similar patient groups using similar outcome instruments [10,11,34,35]. Based on the Hamilton Depression Rating Scale (a 17-item clinician rating form, similar to the QIDS-C) we expect pre-post effect sizes for psychotherapies of depression of *d* = 1.2. A study including a direct comparison of PAT and CBT is not available. Therefore, we used meta-analysis of comparing psychotherapy with psychiatric therapy with depressed out-patients to extrapolate a probable effect size of *d* = 0.50 between treatments of different efficacy at post-treatment. To detect this difference at *α* = 0.025 (two-tailed) with a power of 0.80, a minimum number of 60 patients per cell are required (see Figure1).

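### The fixed 0.025/0.025 split across the two co-primary outcomes is valid but needlessly conservative; Holm's step-down test keeps the same 5% family-wise error and rejects at least as much

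*Protocol article*

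**What the plan says.** Under Secondary analyses the article states: "With two co-primary outcomes, we will conduct the tests at a 0.025 level of significance (two-tailed"). The stated purpose is "to adjust for the multiple comparison issue". The overall level of 0.05 is not written down but follows from 2 x 0.025. No step-down, hierarchical or alpha-recycling rule is given.

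Under Outcome, the primary measures are the clinician-rated QIDS "and the Beck Depression Inventory (BDI-2) one year after initiation of treatment (t4"). The next paragraph of that section also says "Secondary outcome measures include the Beck Depression Inventory (BDI 2 [27"]), so the same scale appears under both headings.

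Under Sample size calculation, the same two-tailed 0.025 is used to "extrapolate a probable effect size of *d* = 0.50 between treatments of different efficacy at post-treatment" and to conclude that, "with a power of 0.80, a minimum number of 60 patients per cell are required". The abstract plans 240 patients, 60 in each of four arms; the Design section says "The trial will include about 360 chronically depressed outpatients", which is about 90 per cell if split evenly.

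**The concern.** Each scale faces 0.025 regardless of the result on the other. Once one scale has shown a difference at 0.025, the 5% family-wise error rate no longer requires the second scale to meet 0.025; 0.05 is enough. The fixed split gives that up.

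What is at stake is the second finding. One scale is rated by an independent clinician and the other by the patient, so a difference on both would be more convincing than a difference on one. A second-scale p-value between 0.025 and 0.05, alongside a clear result on the first, counts as non-significant under the stated rule and as significant under Holm, at the same 5% error rate.

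**Working it through.** **Inputs.** From the article: d = 0.50, two-tailed 0.025 per test, power 0.80, 60 per cell (Sample size calculation); two outcomes at t4 (Outcome); totals of 240 (abstract) and about 360 (Design). Assumed: d = 0.50 on both scales, and a correlation ρ of 0.5 to 0.7 between the two test statistics. The article gives no correlation.

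**1. The article's own figure.** Normal approximation, two equal groups, no covariate:

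n per group = 2 (z₀.₉₈₇₅ + z₀.₈₀)² / d² = 2 (2.2414 + 0.8416)² / 0.25 = 76.04, so 77 (78 by the t-test).

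The stated 60 is not reproduced. With 60 per group the expected test statistic is m = 0.50 × √(60/2) = 2.739, and power is Φ(2.739 − 2.241) = 69% (68% by the t-test).

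**2. Error control.**
- Both null hypotheses true: a false rejection under Holm needs the smaller p-value to be at most 0.025. This is the same event as under the fixed split, so the error rate is identical: 4.65% at ρ = 0.5 and 4.30% at ρ = 0.7.
- One null hypothesis true: a false rejection needs that p-value to be at most 0.05, so its probability cannot exceed 5%. With d = 0.50 on the other scale and 60 per group it is 4.0% at ρ = 0.5 and 3.9% at ρ = 0.7.

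**3. Power.** Let c₁ = 2.2414 (level 0.025) and c₂ = 1.9600 (level 0.05). The gain for a given outcome is

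g = P(c₂ < |Z₁| ≤ c₁ and |Z₂| > c₁).

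- Given outcome: fixed split P(|Z₁| > c₁); Holm adds g.
- Both outcomes: fixed split P(|Z₁| > c₁ and |Z₂| > c₁); Holm adds 2g, because the two effects are taken as equal.
- At least one outcome: P(|Z₁| > c₁ or |Z₂| > c₁) under either rule.

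Example, 60 per group, ρ = 0.5: g = 5.3 points. Given outcome: 69.0 + 5.3 ≈ 74.4%. Both: 54.5 + 2 × 5.3 ≈ 65.2% (differences in the last digit are rounding).

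| Per group | ρ | Given outcome, split → Holm | Both, split → Holm | At least one, either rule |
|---|---|---|---|---|
| 60 | 0.5 | 69.0% → 74.4% | 54.5% → 65.2% | 83.6% |
| 60 | 0.7 | 69.0% → 73.9% | 57.9% → 67.6% | 80.2% |
| 90 | 0.5 | 86.7% → 90.4% | 78.3% → 85.6% | 95.1% |
| 90 | 0.7 | 86.7% → 89.9% | 80.1% → 86.6% | 93.3% |
| 120 | 0.5 | 94.9% → 96.8% | 91.0% → 94.8% | 98.7% |
| 120 | 0.7 | 94.9% → 96.5% | 91.8% → 95.1% | 98.0% |

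The row of 60 is a cell-level comparison under the 240-patient plan, 90 the same under the 360-patient plan, and 120 a comparison of the two treatments pooled over preference and randomization under the 240-patient plan.

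**4. Sensitivity to the correlation.** At 60 per group, as ρ goes from 0 to 0.9, power for a given outcome under Holm goes from 75.4% to 73.0% (69.0% under the split). Power for both rises from 47.7% to 60.3% at ρ = 0, and from 62.7% to 70.7% at ρ = 0.9. There is a gain throughout.

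**The case against.** The strongest reply is that nothing here is wrong. The split sums to 0.05, is simple, and matches the level used for the sample size. An adjustment to 0.025 makes sense only if a difference on either scale is enough, and for that criterion Holm gains nothing. The larger gain, for both outcomes, concerns a criterion that the article nowhere sets; if both were required, no split would be needed and the remedy would be different. All of this stands, and it limits the point to an efficiency gain. It does not remove the point: the article states a definite rule, and another rule with the same error rate is never worse in rejections and sometimes better.

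A second reply is that a step-down rule needs a defined family of tests. BDI-2 is listed as both primary and secondary, and the Statistical analysis section tests treatment, assignment and their dependence on each other without naming one confirmatory contrast. This also stands, and the fix has to cover it.

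A reader might infer that the trial is short of power and that the split is to blame. The documents do not support that. The 69% applies to an unadjusted comparison of 60 with 60. The article plans to adjust for intake symptoms, and a baseline correlation of about √(1 − 60/76.04) = 0.46 would bring the requirement down to 60, although the article states no such value. With 90 per cell or 120 per treatment, power for a given outcome already exceeds 80% under the split.

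One real drawback remains: Holm has no simple matching set of 97.5% simultaneous confidence intervals. The article plans none.

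**Conclusion.** The point holds as a modest improvement that needs no extra patients and no extra alpha. The stated split is valid and conservative, not an error. At d = 0.50 on both scales and an assumed correlation of 0.5 to 0.7, Holm adds about 5 points per outcome and 10 to 11 points for both at 60 per group; 3 to 4 and 6 to 7 points at 90 per group; and about 2 and 3 to 4 points at 120 per treatment. How much it matters therefore depends on which comparison is confirmatory and which total applies.

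Two stronger conclusions should not be drawn. Holm does not make it more likely that the trial shows a difference on at least one scale. Nor does it mend the sample size statement: at 60 per group, power for a given outcome stays below 80% under Holm as well. That 60 per cell does not follow from its stated inputs in an unadjusted comparison is a separate matter.

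**What to change.** Replace the sentence under Secondary analyses with one to this effect: for the single confirmatory comparison of PAT with CBT at t4, the smaller of the two p-values (clinician-rated QIDS, BDI-2) is tested at two-sided 0.025; if it is significant, the other is tested at two-sided 0.05 (Holm); the family-wise error rate is 5%.

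With it:
- Name that contrast, saying whether it is cell-level or pooled over assignment.
- Reconcile the Outcome section, so that BDI-2 at t4 has one status. If it is secondary, there is a single primary test and no split is needed.
- State that a difference on either scale suffices, which the adjustment implies.
- Keep 0.025 as the planning level, since the first step of Holm still requires it.

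The cost is a few lines of text and the forgone simple simultaneous intervals; no data, patients or alpha. The change should be made before any comparative t4 results are seen. The Trial status section reports that recruitment is still under way.

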### Randomization

As Figure1 shows, in a partial randomization preference trial, patients are asked if they have a preference for one specific treatment (PAT or CBT). Treatments are outlined to them in terms of a general description (see box for the instructions). If they articulate a specific preference, they are assigned accordingly (preference arm). If they articulate no specific preference, they are randomized (randomization arm).

### Statistical analysis

The design is an analysis of variance design with repeated measures: The main factor is the form of treatment (CBT or PAT) and assignment (preference or randomization). Four main assessments encompass the treatment phase and follow-up. The variability of intake symptoms is controlled as a covariate. To determine the time factor, ANCOVAs with repeated measures and linear regression with autocorrelated data (compound symmetric covariance structure models) are applied. Dichotomous response scores are examined by tests for frequency distributions and procedures of survival analysis (Coxregression, log-ranktests). It is also tested whether differences between CBT and PAT depend on assignment (preference vs. randomization), that is, if a naturalistic selection brings clearer differences than random assignment.

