So far, the evidence for psychotherapy of depression rests on short-term treatments [6-8]. Unlike the results for the treatment of acute depression, psychotherapy, findings of the effects for chronic depression (dysthymia or major depressive episodes) have been limited [8]. In addition, short-term treatments offered in randomized controlled trials lack external validity. Unlike the treatments performed in clinical trials, psychotherapies in clinical practice throughout Europe are of considerably longer duration (CBT up to 60 sessions, psychodynamic treatment up to 80, psychoanalysis up to 240 to 300 sessions). Positive long-term effects of psychoanalysis and psychoanalytic long-term treatments were shown in a representative, multi-perspective and retrospective study [9]. Yet, up until now, there are no controlled studies available comparing psychoanalysis (PAT) and cognitive behavior therapy (CBT) directly [10,11]. However, a few clinical reports [12] comparing psychoanalytic and cognitive-behavioral long-term therapy exist. They demonstrate that even when psychoanalysts and behavior therapists treat similar disorders with similar success rates, the patients differ in many ways.

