## Discussion

This trial has the major goals: (1) to determine the effectiveness of the two long-term treatments (PAT, CBT) reimbursed in the German healthcare system for chronic depression, and (2) to compare the effects of treatment preference against randomization. It combines the virtues of a randomized controlled (efficacy) trial and a naturalistic approach.

As recent meta-analyses have shown, the treatment of depression by short-term treatments has been plagued by high relapse rates and a lack of lasting effectiveness. Long-term PAT and CBT, however, are not easy to compare, as they differ in frequency (one to three sessions per week), total number of sessions, and duration of treatment (one to three years). We therefore tried to reach comparable doses in the first year of treatment. Initially, psychoanalysts often work with low frequency (≤2 sessions per week) with depressed patients; thus there could be 45 sessions of CBT and up to 80 sessions of PAT in the first year. As our primary outcome is measured at one year (t4), doses of treatment can be compared. When psychoanalytic treatment is continued after one year, dose can be adjusted according to patient need and treatment process. As CBT entails relapse prevention, there will also be an extended treatment duration. In any case, number and timing of sessions will be documented. In this trial, a high quality is assured by an independent assessment.

While patient preferences form one of the three key components of evidence-based medicine, studies on the impact of patient preference on outcome have been scarce. Our design enables us to determine the impact of patient preference on outcome, and we expect a lower attrition rate and a higher effectiveness for preferred vs. randomized assignment.

As this trial has been funded substantially by the German Society for Psychoanalysis, Psychotherapy, Psychosomatics, and Depth Psychology (DGPT), a great effort was made to counteract allegiance effects. The study also is financially supported by the independent, medically oriented Heidehof Foundation (part of the well known Robert Bosch Foundation, Stuttgart). One of the principal investigators (MH) is a renowned cognitive behavior therapist. Data collection, monitoring, and analysis are performed by an independent statistician (BR).

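### The PAT versus CBT comparison is a factor of one model fitted over randomised and self-selected patients, and no section reserves it for the randomised ones

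*Protocol article*

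**What the plan says.** The Design section of the protocol article states "The trial will include about 360 chronically depressed outpatients" and splits them by how they come to treatment: "About 180 patients will have a clear preference foreither PAT or CBT", and "About 180 patients will come without preference and accept to be randomized to either PAT or CBT". The Randomization section confirms the rule: a stated preference determines the therapy, and only patients without one are randomised. The Design section says that the study figure "summarizes the 2 (preference) by 2 (psychotherapies) by 4 (time) factorial design".

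The Statistical analysis section follows that layout: "The main factor is the form of treatment (CBT or PAT) and assignment (preference or randomization"). Intake symptoms are the covariate. It adds a test of the interaction: "It is also tested whether differences between CBT and PAT depend on assignment (preference vs. randomization"), and frames this as asking whether naturalistic selection produces clearer differences.

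Hypothesis A compares the two therapies without limiting the comparison to randomised patients. The co-primary outcomes are QIDS (independent clinician rating) and BDI at t4, each tested at 0.025 two-tailed. The Sample size calculation section asks for 60 patients per cell.

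**The concern.** In a two-by-two model with treatment and assignment as factors, the treatment main effect is an average of the PAT minus CBT difference over the two assignment strata. In the randomised stratum that difference is protected by chance allocation. In the preference stratum it also carries any prognostic difference between people who choose psychoanalytic treatment and people who choose CBT.

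The assignment factor does not help here. It removes the average difference between preference and randomised patients, not the difference between the two kinds of chooser. Intake symptoms remove only what baseline severity explains.

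Hypothesis B adds a second reason not to average. It expects a larger gain from preference in PAT than in CBT, which is the same as expecting a PAT minus CBT difference more favourable to PAT in the preference stratum. On the protocol's own expectation, the averaged effect and the randomised effect are then different quantities, even with no confounding at all.

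At stake is whether the main comparison of the two therapies can be called randomised. Any bias stays the same size as recruitment grows while the standard error shrinks, so more patients make a biased result look firmer.

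**Working it through.** **Inputs from the article.** 180 of 360 patients self-selected (Design); 240 in total with 60 per arm (Abstract); d = 0.50, alpha 0.025 two-tailed, power 0.80, 60 per cell (Sample size calculation). **Assumed:** equal cells, so 60 per cell for 240 or 90 per cell for 360; outcome SD of 1; a residual prognostic gap b between choosers of 0.2 to 0.3 SD, for which the article gives no figure; normal approximation; standard errors not reduced for the covariate.

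**1. The plan's own figure.** n per group = 2(2.241 + 0.842)²/0.50² = 76.04, so 77, not 60. With 60 against 60 the power is about 0.69. Baseline adjustment would bring 76.04 × (1 − ρ²) down to 60 only if ρ were about 0.46, and the article states no such correlation.

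**2. Weight of the self-selected contrast.** 180/360 = 0.5. With equal cells, main effect = (randomised difference + preference difference)/2, so a gap b moves it by b/2: 0.10 SD for b = 0.2 and 0.15 SD for b = 0.3.

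**3. False rejections of the averaged test.** SE = √(1/n per cell): 0.129 for 60 and 0.105 for 90. The rejection probability under no true effect is P(|Z + (b/2)/SE| > 2.241).

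**4. Protection from the interaction test.** SE = √(4/n per cell): 0.258 for 60 and 0.211 for 90. Power at two-sided 0.05 is P(|Z + b/SE| > 1.960).

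| n per cell | b (assumed) | Shift | Rejection rate, nominal 0.025 | Interaction power, 0.05 |
|---|---|---|---|---|
| 60 | 0.2 | 0.10 | 0.07 | 0.12 |
| 60 | 0.3 | 0.15 | 0.14 | 0.21 |
| 90 | 0.2 | 0.10 | 0.10 | 0.16 |
| 90 | 0.3 | 0.15 | 0.21 | 0.30 |

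The interaction test reaches 80% power only at (1.960 + 0.842) × SE, which is about 0.72 SD (60 per cell) or 0.59 SD (90 per cell).

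**5. Power at d = 0.50, alpha 0.025.** Randomised patients only, SE = √(2/n per arm): 0.69 with 60 per arm, 0.87 with 90. Averaged over both strata: 0.95 and 0.99. A randomised-only test needs 77 per arm for 0.80, which is 154 randomised patients.

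**The case against.** The article never says that the reported therapy effect is the one averaged over strata. It lists two factors, and a model with their interaction also yields the randomised contrast. Sizing per cell fits a comparison of two cells at least as well as a main effect. The design is open about being a partially randomised preference trial, and a condensed article may leave detail to a fuller document. All of this is fair. A reader might infer that the plan commits itself to a pooled primary estimate. It does not say so; pooling follows from the model described. What stands is that the described model's treatment factor spans both strata and nothing in the article restricts the comparison.

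A reader might also take the Background as evidence that choosers differ in prognosis. The sentence reads "even when psychoanalysts and behavior therapists treat similar disorders with similar success rates, the patients differ in many ways". It reports a few clinical reports rather than this trial's patients, and it speaks of similar success rates. It makes differences between patients plausible but does not establish prognostic ones, and it gives neither size nor direction. Likewise, the Discussion's claim that "It combines the virtues of a randomized controlled (efficacy) trial and a naturalistic approach" describes the design and says nothing about how the strata are combined.

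The gap is an assumption, and it must be what remains after the planned adjustment for intake symptoms. The weight of one half needs equal cells, which cannot be guaranteed where patients choose.

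Finally, a reader might add a multiplicity charge, since treatment, assignment and interaction can be tested on two outcomes. The article does not say that all of these are confirmatory, and assignment serves its own hypothesis. The two outcomes both measure depression and are unlikely to be independent. No family-wise error figure can be supported.

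**Conclusion.** The concern holds for the analysis as described. The treatment main effect of the stated model gives about half its weight, under equal cells, to a non-randomised contrast adjusted only for intake symptoms. The interaction test is not a safeguard. It does not decide which estimate is reported, it has low power against gaps of the assumed size, and under Hypothesis B a positive result could not tell confounding from a genuine preference effect.

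The rejection rates of 7 to 14% and 10 to 21% illustrate an assumed gap of 0.2 to 0.3 SD. They are not estimates of this trial's error rate: with no residual gap and no true interaction there is no inflation. Nor do the documents support the comforting inference that 60 per cell already secures a randomised-only test, because at the stated alpha it gives about 0.69 rather than 0.80.

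**What to change.** In the Statistical analysis section, name PAT minus CBT at t4 among randomised patients as the confirmatory contrast, for QIDS-C and BDI at 0.025 each. It can be estimated from the same model once the treatment-by-assignment term is included.

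Report the preference-stratum difference separately, adjusted for baseline measures already collected at t0 (for example QIDS-C, BDI-2, CTQ and OPD-2). Label it, and any estimate averaged over strata, as secondary and non-randomised. State that the assignment and interaction tests are secondary.

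The change itself is wording and needs no new data, but it has two costs. Power at d = 0.50 falls from 0.95 or more to about 0.69 with 60 per arm or 0.87 with 90 per arm. The confirmatory result then applies to patients without a preference, a narrower group than the trial sets out to include. The stated power should be restated for this contrast, and the totals of 240 (Abstract) and 360 (Design) reconciled, since they decide whether the 154 randomised patients needed for 0.80 will be available: 120 fall short and 180 suffice.

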## Methods

### Study centers

The study is carried out at the following clinical sites: the Sigmund Freud Institute at Frankfurt, the Department of Psychology at the Frankfurt University, the Department of Psychosomatic Medicine and Psychotherapy at University Medicine Mainz, the Department of Psychology at the University of Mainz, the Department of Psychosomatic Medicine and Psychotherapy at the University Clinic Hamburg-Eppendorf, the Department of Psychosomatic Medicine at University Clinic Benjamin Franklin and clinics in the Theodor-Wenzel-Werk Berlin, and the Department of Psychology at the Free University Berlin. These sites are responsible for screening, information, and independent assessment of all patients treated by licensed psychotherapists (PAT or CBT), either in an outpatient unit or in private practice. We have taken care to include different areas of Germany (middle, and north) and institutions, in order to include a broad range of patients and therapists. The Department of Psychology at the University of Tübingen is responsible for CBT training and supervision at all clinical sites. The center for documentation, statistics, and data analyses at the Ludwig-Maximilians University Munich is an independent site that performs data monitoring, randomization, and statistical evaluation. Patients were recruited through outpatient clinics and private practice. In all cases, assessments are conducted by independent, trained, and supervised clinicians, who are blind to the intervention.

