### Intervention: cognitive behavior therapy

Cognitive and behavior therapy for depression was developed by Beck, Rush, Shaw, and Emery [19] and Lewinsohn, Munoz, Youngren, and Zeiss [20]. Their manuals are adapted and integrated in a widely used and well-accepted CBT for depression [21]. Nearly all licensed behavior therapists are familiar with this manual and material, and have received formal training in using the manual. In general, CBT with depressed patients follows five phases within 25 to 45 sessions:

· Phase 1: Development, biographical information, problem analysis, goals, psychoeducation, rationale for treatment, explanation of intervention steps.

· Phase 2: Behavior oriented interventions, activation, increasing pleasant activities, balance of negative and positive activities, situation analysis, structuring day and week.

· Phase 3: Cognitive interventions, thought control, focus on automatic thoughts and alternatives, influence basic assumptions and schemata.

· Phase 4: Skill training, social skills, problem-solving skills, communication skills, role play, stress management, etc.

· Phase 5: Maintenance, prepare for crisis and beginning depression, relapse prevention, transfer into everyday life.

This basic CBT for depression can be extended for chronic depressed patients by intervention elements and strategies (for example, situational analysis, skill training, disciplined self-disclosure) of cognitive behavioral system of psychotherapy [22]. All the study CBT-therapists are well trained and state licensed. They see patients regularly, either in their own private practice or as therapists in cooperating outpatient units. Furthermore, they all participated in an initiating workshop about CBT of chronic depression and were supervised throughout the study. Supervision was offered at each site by experienced senior behavior therapists. In addition, at each site, additional workshops about CBASP or MBCT, or both, were held for the study therapists. Each therapy session is taped and a selection of tapes of each therapy will be rated to control for adherence to cognitive behavior therapy and for therapists’ competence.

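### The stated model has no site term, so common differences between sites can bias the self-selected contrasts and cost the randomised contrast a little precision

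*Protocol article*

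**What the plan says.** The Statistical analysis section of the protocol article names the factors: "The main factor is the form of treatment (CBT or PAT) and assignment (preference or randomization". It adds time over four main assessments and a test of whether the PAT-CBT difference depends on assignment. One covariate is given: "The variability of intake symptoms is controlled as a covariate". For correlation it says that "linear regression with autocorrelated data (compound symmetric covariance structure models) are applied", which describes repeated measures within a patient. Neither Statistical analysis, Secondary analyses nor Randomization mentions site, either as a model term or as a stratification factor.

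Study centers lists clinical institutions in four cities (Frankfurt, Mainz, Hamburg, Berlin) and gives them these duties: "These sites are responsible for screening, information, and independent assessment of all patients treated by licensed psychotherapists (PAT or CBT". Their diversity, in patients and in those who treat them, is intended: "We have taken care to include different areas of Germany (middle, and north) and institutions, in order to include a broad range of patients and" (the quote stops one word short of the sentence's end). On CBT delivery, Study centers says that "The Department of Psychology at the University of Tübingen is responsible for CBT training and supervision at all clinical sites", while the CBT intervention section says "Supervision was offered at each site by experienced senior behavior therapists" and that "at each site, additional workshops about CBASP or MBCT, or both, were held for the study therapists".

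Design expects about 180 of about 360 patients to have a clear preference. Under Randomization, those patients receive the treatment they prefer; only patients without a preference are randomised.

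**The concern.** Randomisation protects the PAT-CBT contrast only among patients who were randomised. It does not protect PAT versus CBT in the preference stratum, nor preference versus randomisation. The second of these is hypothesis B and one of the two major goals named in the Discussion.

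For site to confound these contrasts, two things must hold together. Sites must differ in 12-month outcome for reasons common to both treatments, such as case mix or how strictly the QIDS-C is rated. And the share choosing PAT, or the share stating a preference, must also differ by site. The article shows neither, but the design allows both: the sites were chosen to be diverse, they run screening, information and rating, and nothing constrains patients' choices to be alike across them. A site difference would then be read as an effect of treatment or of preference.

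**Working it through.** **Inputs from the article.** Planned d = 0.50, two-sided alpha 0.025 and 60 per cell (Sample size calculation). Outcome SD is set to 1. The article gives no between-site variance, no PAT share by site and no recruitment by site. All of these are assumed below.

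**The plan's own figure.** n per cell = 2(z₀.₉₈₇₅ + z₀.₈₀)²/d² = 2(2.241 + 0.842)²/0.25 = 76.04, so 77, not 60. The stated 60 does not reproduce. That is a separate matter; here it only sets the starting power, which at 60 per cell is Φ(0.50 × √30 − 2.241) = Φ(2.739 − 2.241) = 0.690.

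**Self-selected contrast: bias.** Take two equally large groups of sites, A and B, whose outcomes differ by D whatever the treatment. Without a site term:

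bias in PAT − CBT = D × [P(A | PAT) − P(A | CBT)]

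| D (SD) | PAT share A : B | P(A given PAT) | P(A given CBT) | Bias (SD) |
|---|---|---|---|---|
| 0.2 | 60 : 40 | 0.6/1.0 = 0.600 | 0.4/1.0 = 0.400 | 0.04 |
| 0.3 | 70 : 40 | 0.7/1.1 = 0.636 | 0.3/0.9 = 0.333 | 0.09 |
| 0.5 | 80 : 40 | 0.8/1.2 = 0.667 | 0.2/0.8 = 0.250 | 0.21 |

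The middle row is 0.09/0.50, about a fifth of the planned effect. The same formula serves preference versus randomisation, with P(A | preference) and P(A | randomised) in the bracket. The test of whether the PAT-CBT difference depends on assignment subtracts an unbiased randomised contrast from the preference contrast, so it carries the preference-stratum bias in full.

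**Self-selected contrast: false positives.** With 60 per cell the standard error is √(2/60) = 0.183. Rejection of a true null is 1 − Φ(2.241 − b) + Φ(−2.241 − b), where b = bias/0.183. The three rows give b = 0.22, 0.50 and 1.14, and rejection rates of 0.029, 0.044 and 0.136 against a nominal 0.025.

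**A second set of assumptions.** Four equal cities have evenly spaced effects, perfectly aligned with PAT share, and 1 to 10% of variance lies between cities. PAT shares running from 40 to 60% give a bias of 0.03 to 0.09 SD; 30 to 70% gives 0.06 to 0.19 SD; 20 to 80% gives 0.09 to 0.28 SD. Perfect alignment is unfavourable by construction. If choice does not vary by site, the bracket in the formula is zero and so is the bias.

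**Randomised contrast: precision.** If a share ρ of the variance lies between sites, adjustment reduces the residual SD to √(1 − ρ), and power is Φ(2.739/√(1 − ρ) − 2.241).

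| ρ (assumed) | Power at 60 per cell with site | Gain over 0.690 |
|---|---|---|
| 0.01 | 0.695 | 0.5 points |
| 0.02 | 0.700 | 1.0 point |
| 0.05 | 0.715 | 2.5 points |
| 0.10 | 0.741 | 5.0 points |

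**The case against.** The strongest reply is that this is a short journal summary. It does not call its list of terms complete, it leaves the random effects of the mixed models open, and centre adjustment is often left to the full protocol or analysis plan. An analysis plan that is not shown may already include site, and the article cannot settle that. But the article does more than stay silent: it names the factors, the covariate and the covariance structure, and in a partly self-selected multi-site design the model so named is weaker than one with site in it.

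Several further points stand and limit the claim:

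- A reader might infer that CBT content and supervision as a whole differ by site. The article does not support that. It describes one widely used CBT manual and makes one department responsible for CBT training and supervision everywhere. Local supervision is also described, but in content only the add-on workshops are said to vary.
- Differences in the workshops act on CBT patients only. That is variation of the treatment effect between sites, not a common site effect, and an additive site term does not remove it.
- Rater differences cannot act on the BDI-2, which is self-reported. The QIDS-C raters are described as trained, supervised and blind, and the diagnostician also rates the QIDS-C at intake (Table 2), so the covariate absorbs part of any lasting difference between raters or in severity.
- All patients receive brief descriptions of both treatments, which suggests fairly uniform information.
- If preference follows the type of institution, much of that variation may lie within a city, where a city term cannot reach it.

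**Conclusion.** The point holds as a limited one. The model as stated leaves out site although sites screen, inform and rate, and although about half of the patients choose their arm. The preference-stratum PAT-CBT contrast and the preference-randomisation contrast can therefore be biased by common site differences, provided that choice varies by site. The figures of 0.04 to 0.21 SD are illustrations under assumed site differences and PAT shares, not estimates for this trial.

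Two stronger readings are not supported. A reader might infer that the randomised PAT-CBT comparison is biased. It is not: leaving site out costs only about 0.5 to 5 power points for an assumed 1 to 10% between-site variance. A reader might also infer that a site term would make the preference contrasts trustworthy. It would not, because patients still select themselves within each site.

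**What to change.** State in Statistical analysis that study city (Frankfurt, Mainz, Hamburg, Berlin) enters the primary model and all treatment, assignment and interaction models as a fixed effect with four levels. City is preferable to single institutions because institutions within a city may align with treatment type, which would leave sparse or empty cells. Describe the treatment contrast by city without testing it, so that any variation linked to the add-on workshops can be seen. If city was a stratum of the randomisation, the term also matches the analysis to the allocation.

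The cost is one sentence, three degrees of freedom and slightly less precision if the cities do not differ. City should be known for every patient, and recruitment is described as ongoing, so the choice can be fixed before outcomes are analysed. Say in the same place what the term does not remove: patient-level self-selection, differences between institutions within a city, and site differences that act on CBT only. The preference contrasts should still be reported as non-randomised.
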